### Recruitment, inclusion and exclusion criteria

Patients for the AUTHARK study will be recruited from three different sites: (1) the outpatient units of the Department of Child and Adolescent Psychiatry and of the School of Child and Adolescent Behaviour Therapy (AKiP) at the University Hospital Cologne, (2) primary and special education schools and (3) pediatric and psychiatric practices in Cologne, Germany.

Participants will be included if they meet the following inclusion criteria: (1) child age: 6;0 to 12;11 years at T1; (2) clinician-rated diagnosis of ODD/CD based on a structured interview (ILF-EXTERNAL) that is part of the comprehensive Structured Interview for Children and Adolescents according to ICD-10 and DSM-5 from the DISYPS Systems (DISYPS- ILF) [53] at T1; (3) parent-rated ODD/CD symptoms from the parent-rated DISYPS III Symptom Checklist for Disruptive Behaviour Disorder (SCL-DBD parent) [43] with a stanine score of 7 or higher at T1; (4) peer-related aggressive (verbal and/or physical) behavior must be reported by the parents/caregivers at T1; (5) willingness and ability (e.g. sufficient knowledge of German, sufficient competence in using a smartphone) of patient and parents/caregivers to participate in the intervention; (6) children treated with a stable dose of psychotropic medication (e.g. methylphenidate) will be included in the trial. Criteria (2) and (3) will also be evaluated again at T3. If these two criteria no longer apply to the patients at T3, the study participation will be terminated.

The following exclusion criteria will be applied and evaluated at T1: (1) child’s intelligence is below average (IQ < 85) based on a standard intelligence test (German version of the Culture Fair Intelligence Test, Primary Intelligence Scale 1 (CFT 1-R) [54] and Scale 2 (CFT 20-R) [55]; (2) Autism spectrum disorder or other severe comorbid disorder which dominates the clinical picture according to clinical rating; (3) Current or planned inpatient psychotherapy or outpatient behavioral parent management training on a weekly/biweekly basis; (4) Low level of German language skills of the patient or the parents/caregivers.

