### Allocation

Participants will be randomly assigned to either the treatment condition including the AUTHARK app [56] (*n* = 35) or the active control condition, which includes treatment without the AUTHARK app but with paper-and-pencil homework assignments (*n* = 35). We will use computerized block randomization with a block size of 4 and random selections from all 6 permutations. Allocation will only take place after the participants have completed the initial screening, fulfilled all the inclusion criteria and gave their written consent (patients, parents and teachers). The participants will be randomized by the Principal Investigator [name]. The staff members who are also responsible for the recruitment and the initial diagnostics will request randomization. In return, [name] will send a digital answer form to the same staff member, containing the group allocation (experimental or control group). The staff member will then inform the therapist and the family about the treatment intervention.

Due to the nature of the intervention, it will not be possible to blind trial participants, parents/caregivers, and therapists to allocation. However, the parents/caregivers and patients will be blind regarding the specific hypotheses.

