#### Outcomes

##### Primary outcome

Therapy homework adherence (THA) is defined as the relative ratio of completed to requested entries that are implemented in the video diary or the paper-and-pencil diary (which can be completed either independently by the children or with parental support) between the treatment sessions and the independent overall rating of the quality of entries within an assessment week.

The entire study comprises 24 appointments for the children. Starting at the second therapy session, therapy homework will be assigned every other session (sessions 2, 4, 6, 8, 10, 12, 14, 16, 18, 20, 22, 24). Accordingly, the patients will work on the therapy homework a total of 12 times.

For each assignment, patients will be asked to complete either the video diary or the self-observation sheet on five consecutive school days. The relative ratio can be calculated by dividing the number of completed entries through the number of requested entries. The results will range from 0 to 1.

The independent overall rating of the quality of the video diary or the paper–pencil-diary entries is rated on a 4-point Likert scale (0 = poor quality, 1 = low quality, 2 = largely good quality, 3 = good quality). The overall quality includes two specific criteria: (a) the relevance of the content (spoken or written) to the questions asked, and (b) the level of detail of the spoken or written answers. This rating is based on a rating manual specifying the two quality criteria. Five independent raters will rate the video diary and the paper–pencil diary entries. Interrater agreement will be calculated by conducting intraclass correlation (ICC), using a two-way mixed model for consistency and absolute agreement.

In a preliminary analysis of 15 video diary entries, interrater reliability for five independent raters was conducted. The values for consistency were found to be in the “very good” (0.95) range and the values for absolute agreement were found to be in the “average” (0.73) and “good” (0.87) range [60].

The number of completed entries implemented in the video diary or the paper-and-pencil diary and the overall rating of the quality is assessed trough the newly developed Adherence Questionnaire, which is completed by the therapists after every therapy session, but especially in every session that follows a therapy homework week. For example, when therapy homework is assigned in session 2, the therapist will evaluate the results in session 3.

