##### Analyses of primary endpoint

The primary (full) analysis set is derived from the intention-to-treat (ITT) principle (all patients randomized with a valid baseline assessment). Additionally, per protocol analyses will be conducted based on all patients with at least 50% of the planned treatment sessions and a valid follow-up. As primary endpoint, the overall scores on THA will be calculated from the baseline, intermediate, and final assessment points (T1, T2, T3). THA scores assessed after each session will also be included in the analyses. A mixed model repeated measures multivariate analysis of variance will be performed with the between factor Group (smartphone-augmented vs. traditional), the within factor Time (baseline, first treatment phase, intermediate assessment, second treatment phase, final assessment) and the two-way interaction of Group x Time.

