## Discussion

The AUTHARK study will yield information about the effects of smartphone-augmented CBT on the THA compared to conventional paper-and-pencil assignments completed between therapy sessions for children aged 6–12 years with a diagnosis of ODD/CD.

The study will also explore the role of therapy homework as a possible mediator of treatment outcome. Furthermore, the trial will describe possible effects of app-augmented CBT on the symptoms of ODD / CD, ADHD, and other comorbid behavioral or emotional problems; on individually defined problem behaviors; on triggering and maintaining factors of peer- and adult-related aggression (social cognitive information processing, impulse control, social skills, empathy, adaptive and maladaptive strategies for regulation of emotions, problem solving competences); on the children’s quality of life; on the children’s and parents’/caregivers’ level of psychosocial functioning; and on the parents’/caregivers’ and patients’ satisfaction with the treatment.

Since this study is designed as a pilot study, there are some aspects that may prove challenging during the course of the study. One of these aspects is the young age of the children we plan to include. However, our preliminary experience with children in this age range is that even children aged six to seven years are able to handle the smartphones and the requirements of the app. This experience is also supported by the results of a small pilot study that investigated the use of a language app with kindergarten children. The authors reported that children aged three to five years were able to use the app well with support [81]. Moreover, the effects of age on usability and adherence to the intervention will be analyzed.

Another challenge of the study is the risk of bias regarding the outcome ratings. Although participating families will not be informed about the hypotheses of the study, they may conclude from the information letter that the use of the AUTHARK app is an innovation and is expected to result in higher therapy homework adherence. Likewise, the treating therapists cannot be blinded to the intervention. However, the detailed descriptions of quality criteria, on which the rating is based, (see “15”) may reduce the risk of bias. Moreover, in a subsequent main study, an independent blinded evaluation of therapy homework adherence will be considered.

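### The stated primary model has no age term, so the group difference in homework adherence may lose some precision and is open to chance age imbalance

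*Protocol article*

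**What the plan says.** Under Analyses of primary endpoint the model is written out term by term: "A mixed model repeated measures multivariate analysis of variance will be performed with the between factor Group (smartphone-augmented vs. traditional"), a within factor Time with five levels, and "the two-way interaction of Group x Time". No covariate is listed.

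Four other places bear on this:

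- Recruitment, inclusion and exclusion criteria: "child age: 6;0 to 12;11 years at T1". Age is an eligibility criterion, so it is known for every randomised child.
- Allocation: "We will use computerized block randomization with a block size of 4 and random selections from all 6 permutations". No stratification factor is mentioned.
- Primary outcome: the THA score is the completion ratio times a 0-3 quality rating. The rating has two criteria, "the relevance of the content (spoken or written) to the questions asked" and "the level of detail of the spoken or written answers". Entries are ones "which can be completed either independently by the children or with parental support".
- Discussion: the young age of the children is named as a possible challenge, and "the effects of age on usability and adherence to the intervention will be analyzed".

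The research questions in the Background also give age as an example of a moderator or predictor of treatment outcome. The section on predictors and moderators, which concerns ODD/CD symptoms and impairment, does not list the child's age.

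**The concern.** A 6-year-old and a 12-year-old can be expected to differ in how much detail they give, especially in writing, which is what the control diary asks for. If so, part of the between-child spread in THA is age, and the stated model leaves it in the error term. With 35 children per arm and no age stratum, the arms can also differ in mean age by chance, and the single observed THA difference then moves with it.

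Hypothesis 1 asks whether the app arm shows stronger adherence, which is a between-group difference. That is the quantity to which a prognostic covariate could add precision. The pilot is also meant to supply variance estimates for planning the main trial (Sample size), so it matters whether the reported variance is marginal or age-adjusted.

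**Working it through.** **Inputs from the protocol article.** 35 per arm; assumed effect d about 0.4; about 30 per arm recommended for a pilot; dropout 10-15% (all from Sample size); ages 6;0 to 12;11.

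**Assumptions not in the documents.** Two-sided alpha 0.05; one mean THA score per child; ages spread uniformly from 6 to 13; age-THA correlation rho between 0.1 and 0.55.

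**The plan's own figure.** 30/(1 - 0.10) = 33.3, so 34; 30/(1 - 0.15) = 35.3, so 36. The stated 35 per arm lies between. The article states no power for this trial, so there is none to reproduce.

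**Precision.** In SD units the unadjusted standard error of the group difference is sqrt(2/35) = 0.239. Adjusting for age multiplies it by sqrt(1 - rho^2). Approximate power is Phi(0.4/SE - 1.96), which without age is Phi(0.4/0.239 - 1.96) = 0.39.

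**Chance imbalance.** The SD of age is 7/sqrt(12) = 2.02 years. The SE of the difference in mean age is 2.02 x 0.239 = 0.48 years, so the 95% range is +/-0.95 years. P(difference > 0.5 year) = 0.30 and P(> 1 year) = 0.04. An imbalance at the 95% limit shifts the unadjusted d by rho x 1.96 x 0.239 = 0.469 x rho.

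| rho | Variance explained | SE factor | SE reduction | Power at d = 0.4 | Shift in d at 95% limit |
|---|---|---|---|---|---|
| 0.1 | 1% | 0.995 | 0.5% | 0.39 | 0.05 |
| 0.2 | 4% | 0.980 | 2% | 0.40 | 0.09 |
| 0.3 | 9% | 0.954 | 5% | 0.42 | 0.14 |
| 0.4 | 16% | 0.917 | 8% | 0.45 | 0.19 |
| 0.5 | 25% | 0.866 | 13% | 0.49 | 0.23 |
| 0.55 | 30% | 0.837 | 16% | 0.52 | 0.26 |

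**Validity.** A simulation of 10,000 trials per scenario, 35 per arm, compared the two analyses. With no true effect, the unadjusted type I error was 0.050 at rho 0.3 and at rho 0.5. At a true d of 0.4 the mean unadjusted estimate was 0.397-0.398 and the mean adjusted estimate 0.398. Power rose from 0.374 to 0.402 at rho 0.3 and from 0.367 to 0.468 at rho 0.5. The simulation uses t tests, so its power runs slightly below the normal approximation in the table.

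**Which term gains.** Age at T1 is constant within a child. Entered as a main effect with coefficient b, it contributes b x age to every THA score of that child and cancels from any difference between two time points. With complete data, within-child Group x Time contrasts and their standard errors are therefore unchanged. The reductions in the table apply only to the overall group difference.

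**The case against.** **Covariates are often left to the analysis plan.** This is true, the article refers to such a plan for missing data, and that plan is not shown. It may add age, so the list of terms should not be read as ruling covariates out. But the article does write out a primary model, and age is not in it.

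**The age effect is inferred.** This stands. No section says that diary quality depends on developmental level, the rating manual is not shown, and no correlation is given. Parental help is allowed and the app diary is spoken; both could flatten an age gradient. The argument rests mainly on one quality criterion and says nothing about the completion ratio. At a correlation of 0.2 or less, adjustment brings next to nothing.

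**Stronger readings that the documents do not support.** A reader might infer any of the following:

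- That the unadjusted comparison is biased. It is not: randomisation protects it, the error rate holds, and chance imbalance is already reflected in its standard error. The shifts in the table are conditional, go in either direction and average to zero.
- That the protocol expects age to affect adherence. The Discussion plans to analyse age effects, and reports that even six- to seven-year-olds cope with the app.
- That the pilot's variance estimate is inflated. Marginal variance is the right input for an unadjusted main trial, and either variance can be computed from the pilot data whichever primary model is used.
- That age is needed because THA has no baseline. The article lists THA at T1 yet starts homework at session 2. That is a separate inconsistency, and this point does not depend on it.

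**Conclusion.** The point holds as one of efficiency and of robustness to chance imbalance, not as an error of validity. The stated primary model omits a variable that is known for every child, that the sponsor already intends to study in relation to adherence, and that plausibly relates to part of the score. The size of the benefit is uncertain because it rests wholly on an assumed correlation: negligible at 0.1-0.2, modest at 0.3, and useful from about 0.4 upward. Even then, power at d = 0.4 stays near one half on the assumptions above. The article does not say whether Group or Group x Time carries the primary test, and only the former gains.

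**What to change.** - Prespecify age at T1, continuous, as a covariate in the primary mixed model, before outcome data are examined by arm.
- Report the age-adjusted overall group difference as primary and the unadjusted difference as a sensitivity analysis.
- Report both the marginal and the age-adjusted THA variance, so that the main trial can use the one that matches its own analysis.
- State how this relates to the analysis of age and adherence promised in the Discussion.

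The cost is one degree of freedom and a sentence in the analysis plan. No new data are needed and the allocation does not change. If age turns out to be only weakly related to THA, there will be little or no gain.

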In detail, this study will examine the following hypotheses:1) The experimental group (THAV/ScouT + AUTHARK) will show stronger adherence (implementation of therapy homework assignments (THA)) than the control group (THAV/ScouT), as assessed after each therapy session using the Questionnaire for Therapy Adherence [42] (primary outcome).2) The experimental group (THAV/ScouT + AUTHARK) will show a stronger reduction in aggressive symptoms than the control group (THAV/ScouT) (assessed using the parent-, teacher-, and patient-rated DISYPS-III Symptom Checklist for Disruptive Behavior Disorder (SCL-DBD parent, SCL-DBD teacher, SCL-DBD patient (ages 11–18) [43] and using the individual problem list from the THAV program [4]).3) The experimental group (THAV/ScouT + AUTHARK) will show a stronger reduction in comorbid symptoms than the control group (THAV/ScouT) (assessed using the total score of the German version of the Child Behavior Checklist for ages 6–18 (CBCL/6-18R-total) [44], the total score of the German version of the Teacher’s Report Form for Ages 6–18 (TRF/6-18R-total) [45], the total score of the German version of the Youth Self Report for ages 11–18 (YSR/11-18R-total) [46], and the parent-, teacher-, and patient-rated DISYPS-III Symptom Checklist for Attention-Deficit/Hyperactivity Disorder (SCL-ADHD parent, SCL-ADHD teacher, SCL-ADHD patient (ages 11–18) [43]).4) Patients in the experimental group (THAV/ScouT + AUTHARK) will show a stronger improvement in psychological functions that help to reduce aggressive symptoms (social-cognitive information processing, impulse control, social skills, empathy) than patients in the control group (THAV/ScouT) (assessed using the parent- and patient-rated Questionnaire on Aggressive Behavior in Children (FAVK parent, FAVK patient (ages 9–12) [47], the parent- and patient-rated Inventory of Callous-Unemotional Traits (ICU parent, ICU patient (ages 8–12) [48] [49], and a Social Problem-Solving Test for children ages 6–12 (SPST) [7].5) Patients in the experimental group (THAV/ScouT + AUTHARK) will show a stronger improvement regarding psychosocial functioning and quality of life than patients in the control group (ScouT/THAV) (assessed using the parent-rated modified German version of the Weiss Functional Impairment Rating Scale Parent Report (WFIRS-P-M) [6], the revised parent- and patient-rated Questionnaire for Measuring Health-Related Quality of Life in Children and Adolescents KINDL-R parent, KINDL-R patient (ages 7–13) [50], and the parent- and patient-rated Questionnaire for the Assessment of Adaptive and Maladaptive Emotion Regulation Strategies (FRUST parent, FRUST patient (ages 8–12)) [51].6) Patients and parents/caregivers in the experimental group (ScouT/THAV + AUTHARK) will show higher treatment satisfaction than those in the control group (ScouT/THAV) (assessed using the modified German version of the Client Satisfaction Questionnaire (ZUF-8-M) for parents/caregivers and patients [52]).

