## Methods

### Trial design

The AUTHARK study is designed as an interventional randomized controlled study with two parallel treatment arms.

Figure 1 shows the overall design of the AUTHARK study. After the initial screening at T1, patients who meet the inclusion criteria will be randomly assigned to one of the treatment arms. Children in both the experimental group and the control group will receive social skills training (combination of THAV [4] and ScouT [7]). In addition to the treatment, the AUHARK smartphone app will be used in the experimental group. The treatment will be administered in three phases (1–3). Each phase includes eight weekly therapy sessions with the children and two to three sessions with the parents/caregivers. The first treatment phase (1) is followed by an intermediate assessment (T2) with a reduced set of assessment instruments. The second treatment phase (2) is followed by a major assessment (T3). Children who no longer show clinically significant symptoms of ODD/CD at T3 will not receive further therapy but will participate in a first follow-up assessment (T4) eight weeks after T3. Those patients with significant symptoms at T3 will undergo a third treatment phase with a further eight child sessions and two to three caregiver sessions, which will be followed by the T4 assessment. A follow-up evaluation (T5) for all patients will take place one year after T4.

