#### Participant timeline

The individual study duration per patient is between five and seven months. Measurements will take place according to a specific schedule. The trial consists of three general parts: a screening process, the intervention period, and the follow-up assessment. Through an initial investigation using standardized telephone screening, a broad assessment of the inclusion and exclusion criteria will be conducted. Shortly after this initial investigation, the pre-treatment measurement (T1) will occur, which involves a detailed examination of the inclusion and exclusion criteria. After being randomized to the experimental or control group, all patients will undergo a first treatment phase (1), consisting of eight patient sessions and two to three parent/caregiver sessions, followed by an intermediate assessment (T2). Subsequently, another treatment phase (2) will be carried out, followed by a main assessment (T3). Non-responders to the treatment (significant symptoms of OD/CDD at T3 based on the clinician-rated parent interview (ILF-EXTERNAL) [53] and on the parent rating (SCL-DBD) from the DISYPS-III [43]) will participate in a third treatment phase (3), followed by a final assessment (T4). Responders to the treatment (no significant symptoms of ODD/CD at T3) will terminate the study and take part in a first follow-up assessment (T3) eight weeks after their last session. After one year, every family will be asked to complete a follow-up survey (T5).

Therefore, four study visits (T1-T4) will take place for all children and parents/caregivers in order to complete assessments. Additionally, there will be 16 study visits for all children and four to six study visits for all parents/caregivers (treatment phases 1 and 2). Within the group of non-responders after T3, there will be a further eight visits for children and two to three visits for parents/caregivers (treatment phase 3).

At the main assessment points (T1, T3/T4), the primary outcome (THA) and the secondary outcomes will be assessed. At the intermediate assessment (T2), the primary outcome and symptoms of ODD/CD as well as comorbid conditions will be assessed using only parent- and child-report questionnaires and without a clinical interview. The primary outcome will additionally be assessed every two weeks, as the therapist will rate the children’s THA using the Adherence Questionnaire (Fig. 5).

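### The primary model gives homework adherence (THA) a T1 baseline level that cannot exist and T2/T3 levels with no data of their own, and does not say which term tests the level hypothesis

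*Protocol article*

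**What the plan says.** - **Definition.** Under Primary outcome, THA rests on the share of requested diary entries that a child completes between sessions, by video in one arm and on paper in the other, combined with a rating of entry quality. The score is the ratio times the quality rating and runs from 0 to 3.
- **When it first exists.** The same section states: "Starting at the second therapy session, therapy homework will be assigned every other session". Its own example is that "when therapy homework is assigned in session 2, the therapist will evaluate the results in session 3".
- **When T1 is.** Trial design: "After the initial screening at T1, patients who meet the inclusion criteria will be randomly assigned to one of the treatment arms". Participant timeline calls T1 the pre-treatment measurement.
- **Schedule.** Participant timeline nevertheless states: "At the main assessment points (T1, T3/T4), the primary outcome (THA) and the secondary outcomes will be assessed". For T2 it lists THA among measures taken with parent and child questionnaires only.
- **Analysis.** Under Analyses of primary endpoint, "the overall scores on THA will be calculated from the baseline, intermediate, and final assessment points (T1, T2, T3"), and scores recorded after each session are also to enter. The model has a between factor Group and "the within factor Time (baseline, first treatment phase, intermediate assessment, second treatment phase, final assessment) and the two-way interaction of Group x Time".
- **Hypothesis 1 (Background).** "The experimental group (THAV/ScouT + AUTHARK) will show stronger adherence" than the control group, assessed after each therapy session.

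**The concern.** The primary outcome is scheduled and modelled at a visit where it is undefined. At T1 no entries have been requested, so the ratio has no denominator.

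Two more of the five Time levels are also unclear. THA comes only from homework weeks and is recorded by the therapist. The intermediate and final assessments can therefore only be empty or repeat data already counted in the treatment phases.

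Whoever runs the analysis must decide what to do with these levels, and the choice changes the answer. A model that opens with a baseline level also invites reading Group x Time as the treatment effect, whereas Hypothesis 1 is about the level of adherence. At stake are the size of the reported difference, the term that decides the primary question, and the variance estimates the pilot is meant to pass to the confirmatory trial.

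**Working it through.** **Inputs from the protocol (Sample size).** d = 0.4; about 30 children per arm recommended; dropout 10 to 15%; 35 per arm planned. No power is stated for this trial.

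**The protocol's own figure.** 30/(1 − 0.10) = 33.3, so 34. 30/(1 − 0.15) = 35.3, so 36. The planned 35 lies between them, so it reproduces.

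**Assumptions, not in the protocol.** Two-sided alpha 0.05; unit variance and compound symmetry; within-child correlation ρ = 0.3, 0.5, 0.7; a constant app advantage of 0.4 at every on-treatment level; complete data. The four on-treatment levels are taken at face value in cases A and B.

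**Formulas.** With n per arm, m levels, group differences dⱼ and mean difference d̄:
- Group: λ = (n/2)·d̄² / [(1 + (m − 1)ρ)/m], on F(1, 2n − 2).
- Group x Time: λ = (n/2)·Σ(dⱼ − d̄)² / (1 − ρ), on F(m − 1, (m − 1)(2n − 2)).

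**Case A: no T1 level, four on-treatment levels.** d̄ = 0.40 and the Group numerator is 17.5 × 0.16 = 2.80. All dⱼ are equal, so the interaction λ is 0.

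**Case B: a T1 entry with no group difference, varying between children like the other levels.** d̄ = (0 + 4 × 0.40)/5 = 0.32 and the Group numerator is 17.5 × 0.1024 = 1.792. The sum of squared deviations is 0.32² + 4 × 0.08² = 0.128, so the interaction numerator is 17.5 × 0.128 = 2.24.

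| ρ | A: Group λ, power | A: Group x Time power | B: Group λ, power | B: Group x Time λ, power |
|---|---|---|---|---|
| 0.3 | 2.80/0.475 = 5.89, 0.668 | 0.05 | 1.792/0.44 = 4.07, 0.512 | 2.24/0.7 = 3.20, 0.255 |
| 0.5 | 2.80/0.625 = 4.48, 0.550 | 0.05 | 1.792/0.60 = 2.99, 0.399 | 2.24/0.5 = 4.48, 0.351 |
| 0.7 | 2.80/0.775 = 3.61, 0.466 | 0.05 | 1.792/0.76 = 2.36, 0.328 | 2.24/0.3 = 7.47, 0.563 |

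A simulation at ρ = 0.5 (10,000 replicates) agrees: case A Group 0.56, interaction 0.05; case B Group 0.39, interaction 0.35.

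**Case C: exactly zero at T1 for every child.** The averaged difference again falls to 0.32. But each child's five-level mean is now 4/5 of the four-level mean, so its standard error shrinks by the same factor. At ρ = 0.5, λ = 1.792/(0.64 × 0.625) = 4.48, as in case A. The estimate is biased towards zero by one fifth, but the power of the Group test is unchanged.

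**Case D: assignments as the unit.** Assignments at sessions 2, 4, …, 16 number eight, which matches the minimum of eight measurements given under Sample size. With eight levels and the same assumptions, Group power is 0.755/0.595/0.484 and Group x Time again stays at 0.05.

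**The case against.** **The model contains Group.** A reader might infer that the primary analysis would miss a constant app advantage. The protocol does not support that. Group is in the model and tests exactly such an advantage. No change-from-T1 endpoint is defined, and the interaction is not named as the sole test. If an equal T1 value were present, a constant later advantage would itself produce an interaction (power 0.26 to 0.56 in case B). This objection stands in full.

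**The deciding contrast belongs in the analysis plan.** That is fair, and its absence alone would not be a finding. It matters here because the listed Time levels make the choice consequential.

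**Missing data.** A reader might also infer that a multivariate repeated-measures analysis discards every child with one missing level. The protocol does not state complete-case deletion, and Missing values plans multiple imputation with sensitivity analyses. It gives no missingness rate per assignment, so no loss can be calculated. Imputation does not rescue T1, however, because a T1 score is undefined rather than missing.

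**Baseline might mean the first homework week.** The text ties baseline to T1, and the first homework week comes after randomisation with the app already in use, so it would not be a baseline.

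**It is an exploratory pilot without a formal power calculation.** True, so the power figures are illustrative. But the stated objective is to show significantly higher adherence, and the pilot is meant to supply variance estimates for the next trial.

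**Conclusion.** The point holds in limited form. Two sections place THA at T1, where the protocol's own definition and timing make it impossible, and the primary model uses it as a level of Time. The T2 and T3 levels have no THA source separate from the treatment phases. This is a stated, non-executable element of the primary analysis, not a detail left for the analysis plan.

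The size depends on how the gap is filled:
- An equal T1 placeholder lowers the averaged group difference by one fifth, from 0.40 to 0.32.
- Group power falls to 0.51/0.40/0.33 only if that placeholder varies between children as the other levels do. A constant zero biases the estimate without changing the power of the Group test.
- With T1 removed and Group x Time read alone, a constant advantage is detected at the 5% alpha rate. With Group as the test, power is 0.67/0.55/0.47 on four levels.

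All power figures rest on the assumed alpha, correlations, compound symmetry and complete data. The impossibility of a T1 score rests on none of them.

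**What to change.** 1. In Participant timeline and Analyses of primary endpoint, delete THA at T1.
2. Build the Time factor only from on-treatment homework assignments up to T3, with no separate T2 or T3 levels. State whether the session 16 assignment counts, since homework is rated in the session that follows it.
3. Name the Group difference averaged over those assignments, with its 95% confidence interval, as the primary contrast for Hypothesis 1.
4. Report Group x Time as a secondary analysis of whether the difference changes over treatment.

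The cost is rewording of two paragraphs, ideally before adherence is compared between arms. No new data, visits or children are needed.
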